### Blinding

2.8

Because of the add-on study design, the participants and practitioners cannot be blinded. The assessor will be blinded. The treating physician will not assess the outcome measures. The assessor will be instructed to refrain from talking about the treatment in order to maintain blinding. The statistician and data collector will also be blinded.

### Intervention

2.9

#### Study schedule

2.9.1

The study schedule is presented in Table 1. The trial will include a screening phase, treatment phase, and follow-up phase. At the screening visit, participants will sign the informed consent form. The investigator will perform a physical examination, record the medical history, obtain an L-spine X-ray, collect blood samples, record any concomitant treatment history, and use VAS to determine whether the participant is eligible for the clinical trial. If the participant is taking anti-inflammatory drugs or pain killers, we will implement a 2-week washout period. During the 8 weeks of treatment, the patient will visit the facility twice a week (16 visits). Conventional acupuncture treatment will be administered at every visit in both the treatment group and the control group. Eight sessions of TEA will be conducted once a week only in the treatment group (visits 1, 3, 5, 7, 9, 11, 13, 15). On visits 17, the participants will visit the facility 12 weeks after visit 16. VAS scores for pain will be determined on visits 1, 4 (week 2), 8 (week 4), 12 (week 6), 16 (week 8), and 17 (week 20).

**Table 1 T1:**
[figure not shown]
Study schedule.

#### Treatment group intervention

2.9.2

TEA will be applied to the muscles in the low back area using a 29-gauge, 40-mm polydioxanone suture (Hyundae Meditech Co., Weonju, South Korea). A total of 10 points will be assigned to each subject. For the multifidus muscle, the thread will be inserted in a perpendicular direction at EX-B2 points positioned on either side of L4–5 (n = 2) and L5-S1 (n = 2). For the spinal erector muscles, the thread will be inserted in a transverse direction at points located 3 to 4 cm away from the L3 (one on each side, n = 2) and S1 (one on each side, n = 2) spinal processes, toward L1. The thread will be located in the shallow muscle layers. For the lumbar quadrate muscle, the thread will be inserted in a transverse direction at 2 points, from the L4 spinous process toward the bilateral iliac crest. The thread will be located in the shallow muscle layers (Fig. 2).

**Figure 2 F2:**
[figure not shown]
Point location and direction of thread embedding acupuncture for patients with chronic low back pain. (1) Multifidus muscle: Perpendicular insertion at EX-B2 points positioned on either side of L4–5 (n = 2) and L5-S1 (n = 2). (2) Spinal erector muscles: Transverse insertion at points located 3–4 cm from the L3 (one on each side, n = 2) and S1 spinous processes (one on each side, n = 2), toward L1. The thread will be located in the shallow muscle layers. (3) Lumbar quadrate muscle: Transverse insertion at 2 points, from the L4 spinous process toward the bilateral iliac crest. The thread will be located in the shallow muscle layers.

In the treatment group, conventional acupuncture treatment will be administered immediately after TEA. Sterilized stainless steel needles (DB108C; Dongbang Medical Co., Boryung-si, South Korea) measuring 0.25 mm in width and 40 mm in length will be inserted at 10 local and 4 distal acupuncture points. The 10 local acupuncture points are as follows: GV3, EX-B5, and bilateral BL23, BL24, BL25, and BL26. The 4 distal acupuncture points are as follows: bilateral BL40 and BL60. Details about the treatment group intervention are described in the Standards for Reporting Interventions in Clinical Trials of Acupuncture (STRICTA) checklist in Table 2.^[17]^

**Table 2 T2:**
[figure not shown]
Details of acupuncture treatments for chronic low back pain, based on the STRICTA 2010 checklist.

#### Control group intervention

2.9.3

The control group patients will receive conventional acupuncture treatment following the same protocol used for the treatment group. TEA will not be administered.

#### Concomitant treatment

2.9.4

Other interventions such as medications, injections, physical therapy, surgical procedures, acupuncture, cupping, and moxibustion will not be permitted during the 8-week treatment period (not applicable to the follow-up phase). However, any concomitant medications taken by the subject within 4 weeks before trial participation, which will not affect the interpretation of the trial outcomes, will be allowed at the discretion of the investigator.

### Outcome measures: primary endpoint

2.10

The primary outcome of our study will be the change in the VAS score for pain from baseline (visit 1) to treatment completion (week 8, visit 16).^[18]^ The patient will quantify the pain intensity by marking the most relevant point on a 100-mm horizontal line anchored by 2 descriptors: 100, representing the “worst imaginable pain,” and 0, representing “no pain.”

### Outcome measures: secondary endpoints

2.11

#### Pain

2.11.1

Every change in the VAS score between baseline (visit 1) and week 2 (visit 4), week 4 (visit 8), week 6 (visit 12), and 3 months after treatment completion (visit 17).

#### Clinical relevance

2.11.2

The minimal clinical important difference (MCID) in the VAS score for chronic low back pain was defined as a decrease of 20 mm.^[19]^ The proportion of patients showing a VAS score decrease of >20 mm (MCID) was compared between the treatment and control groups at week 2 (visit 4), week 4 (visit 8), week 6 (visit 12), week 8 (visit 16), and 3 months after treatment completion (visit 17). The proportion of patients with a VAS score decrease of >30% and >50% relative to the baseline score will also be compared.

#### Disability level

2.11.3

The Korean version of the Roland and Morris Disability Questionnaire (RMDQ) will be used to assess disability due to back pain.^[20]^ The change in the RMDQ score at week 2 (visit 4), week 4 (visit 8), week 6 (visit 12), week 8 (visit 16), and 3 months after treatment completion (visit 17) will be compared between the 2 groups. RMDQ comprises 24 questionnaires, and a higher score indicates greater disability.

#### Quality of life

2.11.4

The 3-level version of Euroqol-5D (EQ-5D-3L) will be used to assess the quality of life.^[20]^ The change in the EQ-5D-3L score at week 2 (visit 4), week 4 (visit 8), week 6 (visit 12), week 8 (visit 16), and 3 months after treatment completion (visit 17) will be compared between the 2 groups. The patients will rate their quality of life in 5 categories using a 3-point scale.

#### Global assessment

2.11.5

The Patient Global Impression of Change (PGIC) score will be used for the global assessment of back pain. PGIC assesses the perceived health status of patients on a 7-point Likert scale ranging from 1 (very much worse) to 7 (very much improved). Grade 4 represents no change.^[21]^ The change in the PGIC score at week 2 (visit 4), week 4 (visit 8), week 6 (visit 12), week 8 (visit 16), and 3 months after treatment completion (visit 17) will be compared between groups.

#### Economic analysis

2.11.6

Cost–benefit and cost-effectiveness studies will be simultaneously conducted. Cost data will be collected using a separate economic analysis case report form (CRF). The medical cost will include the official medical cost (paid by the patient to the hospital) and the unofficial medical cost, which includes the cost of over-the-counter drugs, health foods, medical devices, and other requirements. The nonmedical cost includes the transportation cost, care cost, and time cost. The work productivity lost will also be assessed.

#### Credibility test

2.11.7

The credibility of TEA will be assessed using the Credibility/Expectancy questionnaire at the screening visit. It assesses the credibility and expectancy of the treatment on a 9-point numeric rating scale, with a higher score indicating higher expectancy and credibility.^[22]^

### Safety assessment

2.12

Physical examinations will be performed and vital signs and adverse events will be checked at every visit. A pregnancy test will be conducted at the screening visit. To examine the safety of TEA, a blood test will be conducted at visit 1 and visit 16. The red blood cell (RBC) count, white blood cell (WBC) count, hemoglobin level, hematocrit value, erythrocyte sedimentation rate (ESR), platelet count, aspartate aminotransferase (AST) level, alanine aminotransferase (ALT) level, blood urea nitrogen (BUN) level, creatinine level, electrolyte (Na, K, Cl) level, and C-reactive protein (CRP) level will be assessed. Adverse events will be assessed according to the Standardizing Assessment and Reporting of Adverse Effects in Rheumatology Clinical Trials II: The Rheumatology Common Toxicity Criteria v.2.0. (RCTC v.2.0).^[23]^ Any adverse event during the clinical trial will be recorded and assessed in CRF. The adverse event occurrence ratio will be calculated. Adverse events associated with the intervention will be monitored and appropriately handled.

### Data management and quality control

2.13

CRC will collect data on a paper CRF. Data will be collected according to a preapproved study protocol. To maintain confidentiality, all original source documents, including medical records, questionnaires, consent forms, and other relevant records will be stored at each site in a locked cabinet or a password-protected computer that can be accessed only by an authorized individual. The data will be stored for 3 years after study completion.

Any protocol revision will be handled by Kyung Hee University Korean Medicine Hospital, which will serve as a central coordinating facility. An independent clinical research associate (CRA) will conduct monitoring at each site and ensure that the rights of the subjects are protected, and the clinical trial is conducted in accordance with the research protocol. CRA will monitor the data quality, protocol compliance, informed consent forms, recruitment status, data collection, CRFs, and other relevant documents and processes. Regular audits will be conducted by the Ministry of Food & Drug Safety (MFDS) in Korea. All practitioners and investigators have gone through a good clinical practice training course. To enhance the quality of TEA, it will be performed by a practitioner with >10 years of experience.

### Sample size calculation

2.14

Sample size calculation was performed to determine the appropriate number of participants. The primary outcome will be the change in the VAS score from visit 1 to visit 16 in the treatment and control groups. To our knowledge, no study has investigated the effects of TEA combined with conventional acupuncture treatment. A previous clinical trial evaluated the effects of TEA and sham TEA administered for 4 weeks.^[24]^ The change in the VAS score after treatment (week 4) was 1.85 ± 0.86 in the treatment group and 0.5 ± 0.80 in the control group. The required number of participants per group was 11, considering a 2-tailed test with a 1:1 allocation ratio, a superiority trial, a test power of 95% (1-β), and a significance level of 5% (α). After considering a 40% dropout rate, we calculated the sample size for our study to be 19 patients per group. Thus, a total of 38 participants will be required.

### Statistical analysis

2.15

Data will be expressed as means and standard deviations for continuous variables and frequencies and ratios (%) for categorical variables. The patients’ baseline characteristics will be compared using an independent *t* test or the Wilcoxon rank-sum test for continuous variables and a χ^2^ test or Fisher exact test for categorical variables. If there is a significant difference in the baseline characteristics between groups, analysis of covariance will be used for efficacy analysis, which will include both a full analysis set (FAS) and a per-protocol set (PPS). FAS will be used for the main analysis and PPS will be used for subanalysis of sensitivity. FAS will include patients who will receive at least 1 session of treatment and will undergo at least 1 pain assessment using VAS after treatment. FAS will not include participants who do not meet the eligibility criteria, those who do not receive any treatment, or those whose data are not acquired after randomization. PPS will include patients who will receive at least 12 sessions of treatment (75% compliance rate), those who undergo pain assessment using VAS at visit 16, and those who will complete the clinical trial without major protocol violation. In the primary outcome analysis, the change in the VAS score from visit 1 to visit 16 will be compared between the treatment group and the control group using an independent *t* test or the Wilcoxon rank-sum test according to normality. In the secondary outcome analysis of continuous variables, a *t* test or the Wilcoxon rank-sum test will be applied according to normality. In the secondary outcome analysis of categorical variables, a χ^2^ test or Fisher exact test will be applied. In safety analysis, the total adverse event ratio and adverse event ratio associated with TEA will be compared using a χ^2^ test or Fisher exact test. The last observation carried forward method will be used for missing data. The level of significance will be 5% (2-tailed test). No correction method will be applied for multiple comparisons in the secondary outcome analysis.

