**Methods::**

This randomized, controlled, assessor-blinded, 2-armed, parallel, multicenter clinical trial will include 38 outpatients with chronic low back pain recruited from 4 traditional Korean Medicine hospitals. The patients will be randomly allocated to a treatment group (conventional acupuncture + thread embedding acupuncture) and a control group (only conventional acupuncture) in a 1:1 ratio. The treatment group patients will receive thread embedding acupuncture treatment at 10 acupuncture points (multifidus muscle, 4 points; spinal erector muscles, four points; lumbar quadrate muscle, 2 points) once a week for 8 weeks (8 sessions). In addition, all patients will receive conventional acupuncture treatment at 14 acupuncture points (GV3, EX-B5, and bilateral BL23, BL24, BL25, BL26, BL40, and BL60) twice a week for 8 weeks (16 sessions). The primary outcome will be the change in the visual analog scale score from visit 1 to visit 16, analyzed by independent *t* tests, in both groups. The groups will also be compared with regard to the clinical relevance (minimal clinically important difference), quality of life (3-level version of Euroqol-5D), disability level (Roland and Morris Disability Questionnaire), global assessment (patient global impression of change), and safety. Cost data for cost–benefit and cost-effectiveness analyses will be collected.

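### Adjustment for baseline pain in the primary analysis hangs on baseline significance tests, so baseline VAS is almost never adjusted for on its own account; a pre-specified ANCOVA would be a free improvement

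*Protocol article*

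**What the plan says.** The primary endpoint is the change in VAS from visit 1 to visit 16 (section 2.10). Section 2.15 first sets out between-group tests at baseline: "baseline characteristics will be compared using an independent *t* test or the Wilcoxon rank-sum test for continuous variables", with a χ² or Fisher test for categorical variables. It then makes the efficacy model depend on them: "If there is a significant difference in the baseline characteristics between groups, analysis of covariance will be used for efficacy analysis". It names neither the characteristics that count nor the covariates that would enter. The primary change score is otherwise compared "using an independent *t* test or the Wilcoxon rank-sum test according to normality". The abstract mentions only the t test. Nothing in the article makes baseline VAS a covariate regardless of the baseline tests.

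**The concern.** In a randomised trial a baseline p value reflects chance. It does not show whether a variable predicts the outcome, which is what decides whether adjusting for it helps. Visit-1 VAS is measured on everyone and is the natural covariate, yet under this rule it is used only when its own chance imbalance is large, or when another variable triggers ANCOVA and VAS happens to be included. At stake are some precision, the accuracy of the estimate when the arms start at somewhat different pain levels, and having one analysis fixed in advance for the single primary comparison of a 38-patient trial.

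**Working it through.** **Inputs.** Section 2.14 says that the VAS change in the planning trial "was 1.85 ± 0.86 in the treatment group and 0.5 ± 0.80 in the control group". It uses two-sided α of 5%, 95% power, 11 per group evaluable, and 19 per group after 40% dropout. The article gives no baseline SD and no correlation ρ between visit-1 and visit-16 VAS, so ρ = 0.3, 0.5 and 0.7 are assumed throughout.

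**The plan's own figure.** Difference 1.85 − 0.5 = 1.35. Pooled SD = √[(0.86² + 0.80²)/2] = 0.8305. Standardised effect 1.35/0.8305 = 1.625. Exact t-test power is 0.930 at 10 per group and 0.952 at 11, so 11 is right, and 11/0.6 rounds up to 19. The sample size reproduces.

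**How often the trigger fires.** Baseline VAS alone: 5% by construction (simulated 4.9 to 5.1%). Any of k independent baseline variables: 1 − 0.95^k, which is 23% for k = 5 and 40% for k = 10. The article gives no count, so k is an assumption.

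**What an untriggered imbalance does.** A change score subtracts baseline with slope 1, whereas with equal SDs the regression slope is ρ. A chance baseline difference D therefore shifts the change contrast by (1 − ρ)D, in favour of the arm that started with more pain. For D = 8 mm:

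- ρ = 0.3: 0.7 × 8 = 5.6 mm
- ρ = 0.5: 0.5 × 8 = 4.0 mm
- ρ = 0.7: 0.3 × 8 = 2.4 mm

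With an assumed baseline SD of 15 mm and 19 per arm, significance needs 2.028 × 15 × √(2/19) = 9.9 mm, so 8 mm (t = 1.64, p ≈ 0.11) triggers nothing. Given that imbalance and no treatment effect, the change-score test rejects in about 11%, 9% and 8% of trials.

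The SD matters here: 8 mm is non-significant at 19 per arm only if the baseline SD exceeds 8/0.658 = 12.2 mm. Taking the section 2.14 change SD instead, with equal SDs, the baseline SD is 0.8305/√[2(1 − ρ)] = 0.70, 0.83 and 1.07 units. The largest untriggered imbalance at 19 per arm is 0.658 times that (0.46, 0.55, 0.71), with a shift of (1 − ρ) times that (0.32, 0.27, 0.21), against a planned effect of 1.35.

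**Efficiency.** With equal SDs, the ratio of ANCOVA variance to change-score variance is (1 − ρ²)/[2(1 − ρ)] = (1 + ρ)/2, that is 0.65, 0.75 and 0.85. The table gives simulated power (200,000 trials per cell, change SD 0.8305) for ρ = 0.3 / 0.5 / 0.7. The plan's rule is simulated as ANCOVA only if baseline VAS has p < 0.05.

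| True effect | n per arm | Plan's rule | Pre-specified ANCOVA | Loss (points) |
|---|---|---|---|---|
| 1.35 (planned) | 11 | 95.7 / 95.5 / 95.1% | 99.1 / 98.1 / 96.8% | 3.4 / 2.6 / 1.6 |
| 1.35 | 19 | 99.9 / 99.9 / 99.9% | 100.0 / 100.0 / 99.9% | about 0.1 |
| 0.675 (half) | 11 | 44.3 / 44.1 / 43.9% | 59.0 / 53.2 / 48.1% | 14.8 / 9.1 / 4.3 |
| 0.675 | 19 | 69.5 / 69.2 / 68.6% | 84.5 / 79.3 / 74.1% | 15.0 / 10.0 / 5.5 |

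**Unequal SDs.** With baseline SD 15 and follow-up SD 20 mm (assumed), the change variance is 625 − 600ρ and the ANCOVA variance is 400(1 − ρ²). At ρ = 0.3 the ratio is 364/445 = 0.82, at 0.5 it is 300/325 = 0.92, and at 0.7 it is 204/205 = 1.00. In the last case the shift from an 8 mm imbalance also falls, to 8 × (1 − 0.7 × 20/15) = 0.5 mm.

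**Type I error over all trials.** The baseline-gated rule gives 4.1 to 4.6%. A normality switch (Shapiro-Wilk gate, 6,000 trials per cell, normal and skewed data) gives 4.7 to 5.3%.

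**The case against.** The strongest reply is that on the protocol's own planning figures the rule costs almost nothing: a few points of power at 11 per arm and a negligible amount at 19. That stands. A much larger loss, for example 63% against 80% power at ρ = 0.3, appears only if the planned difference is read as 13.5 mm and paired with an assumed SD of 15 mm, which gives a change SD well above the one in section 2.14. The document does not support offering that as the expected cost. The gain is also fragile: entry requires VAS beyond 40 mm (section 2.4), which narrows the baseline spread, so a larger follow-up SD is plausible.

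A reader might infer that letting the data choose the test inflates the false-positive rate. It does not. Over all trials the rule is slightly conservative, and the 8 to 11% figures hold only given a particular imbalance. A reader might also infer that a non-significant VAS imbalance goes uncorrected. For baseline VAS that is wrong: the change score corrects too much.

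Nor does the abstract contradict section 2.15. Naming only the t test is ordinary condensation. The normality switch is a minor matter, and the normality criterion and covariate list may stand in a fuller document that is not shown.

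What remains is a rule that the article states outright. Further detail elsewhere could name covariates, but it could not make adjustment unconditional without departing from this text. Section 3 concedes that the planning trial lasted 4 weeks and used a sham comparator, so the planned effect is not assured.

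**Conclusion.** The point holds as a recommended improvement and not as a threat to validity. Conditioning ANCOVA on baseline significance means that visit-1 VAS is left out of the model in nearly all trials unless some other variable brings it in. When the arms differ in baseline pain without reaching significance, the change score moves the estimate towards the arm that started worse. The power cost is about 2 to 3 points at 11 per arm and under 1 point at 19 if section 2.14 is right. It is about 6 to 15 points at 19 per arm if the effect is half that size, and nil if follow-up SD clearly exceeds baseline SD and the correlation is high. These figures rest on the assumed correlations and, except in the last case, on equal SDs. The chance of an irrelevant trigger rests on an assumed number of independent baseline tests. The change should be made, but the trial is not unsound without it.

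**What to change.** In section 2.15, delete the baseline-significance trigger and fix one primary analysis: ANCOVA of visit-16 VAS (or of the change) on treatment, with visit-1 VAS and hospital as covariates, reporting the adjusted difference and its 95% CI. Hospital belongs in the model because section 2.7 creates a separate randomisation table for each one. Keep the t test and Wilcoxon test as sensitivity analyses, report baseline characteristics descriptively, and align the abstract. The cost is wording: no extra patients, visits or data, provided it is settled before the data are unblinded.

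### The per-protocol set for the week-8 primary endpoint requires completion of the whole trial, so a patient with adequate treatment and a visit 16 VAS is excluded for missing visit 17, 12 weeks later (minor)

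*Protocol article*

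**What the plan says.** Section 2.10 defines the primary outcome as the "change in the VAS score for pain from baseline (visit 1) to treatment completion (week 8, visit 16", so the endpoint is fully observed at week 8.

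Section 2.15 sets three joint conditions for the PPS. The first is exposure: "PPS will include patients who will receive at least 12 sessions of treatment (75% compliance rate". The other two concern assessment and completion: "those who undergo pain assessment using VAS at visit 16, and those who will complete the clinical trial without major protocol violation". The role of the set is also stated: "FAS will be used for the main analysis and PPS will be used for subanalysis of sensitivity". No other sensitivity analysis of the primary outcome is named.

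Section 2.9.1 says what the trial consists of: "The trial will include a screening phase, treatment phase, and follow-up phase". It also gives the date of the last visit: "On visits 17, the participants will visit the facility 12 weeks after visit 16". That is week 20. Sections 2.11.1 to 2.11.5 list secondary outcomes at that visit; 2.11.1, for example, places it "3 months after treatment completion (visit 17".

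**The concern.** The PPS rule uses two different end dates for one population. One is visit 16, where the primary endpoint is measured. The other is the end of the trial, which on the document's own description is visit 17. A PPS analysis is meant to show whether the week-8 result holds among patients who followed the treatment plan. Attendance 12 weeks after that result was recorded is not part of following the treatment being compared.

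Two things are at stake, both confined to the sensitivity analysis. Observed week-8 values are left out for no reason connected with adherence, in a trial of 38 patients where a few exclusions per group are visible. The exclusion is also made on a variable that could depend on arm and on the week-8 result: sections 2.8 and 3 state that participants are not blinded, and patients who did poorly may be less or more inclined to come back. If FAS and PPS disagreed, visit 17 attendance would be one possible explanation, and it could not be separated from adherence.

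**Working it through.** **Step 1. What completion means in this document.**

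| Place | Term | Time it refers to |
|---|---|---|
| 2.10, primary endpoint | treatment completion | week 8, visit 16 |
| 2.11.1 to 2.11.5, secondary endpoints | treatment completion | the point from which visit 17 is counted, 3 months later |
| 2.9.1, study schedule | the trial | screening, treatment and follow-up phases, ending at visit 17, week 20 |
| 2.15, PPS | completion of the clinical trial | not defined separately |

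The article has its own term for week 8 and does not use it in the PPS rule. Nothing in it limits completion to visit 16 or defines a separate PPS for the week-8 endpoint.

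**Step 2. Apply the rule to one patient.** Take a patient with 16 of 16 sessions, a VAS at visit 16, no violation, and no visit 17. The session condition is met (16 ≥ 12) and the visit 16 VAS condition is met. Trial completion is not met. The patient leaves the PPS for an endpoint observed 12 weeks before the missed visit.

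The exclusion would come mainly from missing visit 17 or withdrawing during follow-up. Other treatment in that period is not a violation, since section 2.9.4 says such treatment "will not be permitted during the 8-week treatment period (not applicable to the follow-up phase".

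**Step 3. Reproduce the sample size, to see what the 40% dropout refers to.** Inputs from 2.14: changes of 1.85 ± 0.86 and 0.5 ± 0.80, two-sided 5%, power 95%, 1:1 allocation.

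- Difference: 1.85 − 0.5 = 1.35.
- Pooled SD: √((0.86² + 0.80²)/2) = 0.8305.
- Standardised effect: 1.35/0.8305 = 1.625.
- Exact t-test power (noncentral t): 0.930 at 10 per group and 0.952 at 11 per group, so 11 per group.
- Dropout: 11/(1 − 0.40) = 18.3, so 19 per group and 38 in total.

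The stated figures reproduce. Section 2.14 names the visit 1 to visit 16 change as the outcome being sized, so the 40% is an allowance for loss before visit 16. The article gives no rate for loss between visits 16 and 17.

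**Step 4. Illustration under assumed later loss.** If the whole 40% is lost by visit 16, 19 × 0.60 = 11.4 per group have the week-8 VAS. Assume a fraction p of these miss visit 17. The PPS is then 11.4 × (1 − p), and its standard error rises by the factor 1/√(1 − p).

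| Assumed p | PPS per group | SE factor | Power at the planning effect (whole n) |
|---|---|---|---|
| 0% | 11.4 | 1.00 | 0.95 (n = 11) |
| 10% | 10.3 | 1.05 | 0.93 (n = 10) |
| 20% | 9.1 | 1.12 | 0.90 (n = 9) |
| 30% | 8.0 | 1.20 | 0.86 (n = 8) |

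If instead 20% are lost before visit 16, 15.2 per group would fall to 13.7, 12.2 or 10.6. The values of p are assumptions; none comes from the documents. Patients who fail another PPS condition are ignored here.

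**The case against.** **The phrase may have been meant more narrowly.** Trial completion is not expressly defined, the article condenses a fuller protocol, and the separate visit 16 VAS condition suggests that week 8 was the intended anchor. The clause's main work may be to exclude major violations. This is fair as a guess at intent, but the text does not say it. If the narrower meaning was intended, the same sentence needs the same correction, because membership of the set would otherwise be decided by interpretation. This is a rule that is stated, not a detail left open.

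**One trial-wide PPS is a usable convention.** The same set serves the visit 17 outcomes, where completion to week 20 is relevant. That stands, and the fix keeps the requirement there. It does not justify the requirement at week 8.

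**The main analysis is untouched.** This stands in full. The FAS needs one session and one post-treatment VAS, so a patient who misses visit 17 stays in it with the observed week-8 value.

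**Stronger readings that the documents do not support.** A reader might spread the 40% dropout evenly in hazard over 20 weeks: 38 × 0.60^(8/20) = 31.0 reach visit 16 and 38 × 0.60 = 22.8 reach visit 17, so about 8 patients (21% of 38) are discarded and the standard error rises by √(0.815/0.60) = 1.17, or 17%. That conflicts with 2.14, which applies the 40% to the visit 16 endpoint. On the plan's own allowance, about 23 of 38 already remain at visit 16.

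A reader might also infer that the PPS estimate would be badly biased. With a true difference of 5 mm, SD 20 mm, and control patients only returning at 60% if they improved by at most 20 mm and at 85% otherwise, the PPS difference is about 2.4 mm. Those inputs are chosen, not taken from the plan. If both arms select alike, the result is about 4.7 mm. With the planning figures in 2.14, read on an assumed 0 to 10 scale as 18.5 and 5 mm with SD about 8 mm, the same one-arm rule gives about 13.3 mm against a true 13.5 mm.

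**Conclusion.** The point holds as a minor one. On the wording of 2.15 read with 2.9.1 and 2.10, the PPS for the week-8 primary endpoint excludes patients with adequate treatment and an observed endpoint because they miss a visit 12 weeks later. This makes the only named sensitivity analysis less precise and harder to interpret. It does not touch the main analysis.

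The size is not computable from the documents. The reduction to about 10.3 to 8.0 per group rests on two assumptions: that 11.4 per group reach visit 16, and that 10% to 30% of them then miss visit 17. Bias from visit 17 attendance is possible because participants know their allocation, but its size is unknown and no figure for it should be quoted as expected.

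**What to change.** In 2.15, tie the completion clause to the endpoint analysed. For the primary outcome and all outcomes up to week 8, replace the final PPS condition with: *complete the treatment period through visit 16 without major protocol violation up to visit 16*. Require visit 17 only for the PPS analysis of visit 17 outcomes. The session and visit 16 VAS conditions can stay as they are.

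The change is one sentence of analysis wording, to be made before unblinding. It needs no new data, patients or procedures. The small downside is that the PPS will differ in size between the week-8 and visit 17 analyses, and both sizes must be reported.
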